**Fig. 1 Fig1:**
[figure not shown]
The study period

**Fig. 2 Fig2:**
[figure not shown]
The study procedure

### Study setting and recruitment

The experiment will be conducted in the Department of Pulmonary Diseases of the First Affiliated Hospital of Jiangxi University of Traditional Chinese Medicine. Relevant recruitment information will be announced through multiple social media and municipal advertisements. Through formal and informal invitations, participants’ names, ages, telephone numbers, and other relevant information will be registered to facilitate further screening. All willing to participate in the study of the participants will receive our leaflet, we will related information and the advantage of the participants of the study, the rights, interests, responsibilities, and obligations to print on the leaflets in order to effectively inform participants, we will be the first time, in the form of telephone invite all participants to the hospital to complete the test screening, The relevant baseline data and physical examination information of participants who met the inclusion criteria are recorded promptly. Participants will be recruited continuously until the required sample size is reached.

### Sample size

6MWT is the most commonly used outcome indicator in pulmonary rehabilitation (PR) and can be used for sample size estimation. In 6MWT, the minimum difference (miniDIFF) between different groups is 54 m, and the baseline standard deviation (SD) is 57 m. Given a two-tailed 0.05 and a power of 80%, the minimal sample size for each group is 19. To compensate for the expected loss of participants, an adjusted sample size of 27 could be acquired for each group, and 140 patients could be recruited, assuming a roll-out rate of 30%.

### Participants

All participants are stable IPF patients will be recruited from the Department of Respiratory Medicine at the First Affiliated Hospital of Jiangxi University of Traditional Chinese Medicine. Potential participants will be screened through the hospital’s clinical database to determine whether they will be contacted by phone or in-person for the study. All participants who signed the consent form will be evaluated by an assessor with their eyes covered. Participants who meet the relevant eligibility criteria will have their demographic, anthropometric, and questionnaire information recorded, and they will be randomly assigned to each group.

Diagnosis of IPF will be confirmed according to the Global IPF Initiative (GOLD) standard. The criteria include: (1) Age between 35 and 80; (2) The clinical symptoms are stable in the last two months; (3) Patients diagnosed with IPF who satisfied the diagnostic criteria of ATS/ERS/JRS/ALAT 2018 [According to past medical history, laboratory tests and HRCT (typical UIP and Probable UIP)]; (4) Have not participated in systematic or intermittent training for another sport in the past six months (no more than twice a week); (5) No other disabling diseases (e.g. stroke, Parkinson’s disease, etc.); (6) Patients who agree to sign written informed consent.

Among the exclusion criteria are the following: (1) other chronic respiratory diseases; (2) serious complications, such as cardiovascular, liver, or kidney disease; (3) in patients whose condition is rapidly deteriorating or urgently requiring other medication management; (4) skeletal muscle diseases or other diseases that may affect muscle strength assessment.

### Randomization and concealed allocation

Prior to the baseline assessment, participants will be randomized into five groups: CG, IG, TG, RG, and IRG. The allocation sequence will use “study randomized” transcendental prior distribution, the random number generator is (https://www.randomizer.org/) online random number generator, and the participation of participant recruitment assessment or not engage in the researchers. Concealed allocation will be achieved using sequentially numbered, sealed, and opaque envelopes kept in security cabinets that can only be opened by specifically authorized staff.

### Blinding (masking)

The outpatient doctors ([name] and [name]) will conduct the initial assessment of the patients from the outpatient department, enter the collected information independently, and compare the information to find errors and correct them in time. The treating physicians ([name] and [name]) are blinded to the initial evaluations and group assignments. In addition to counting and analyzing the data independently of the multiple physicians administering the intervention, the statistical analysis team will be blind to the group assignments and the purpose of the study. Unmasking occurred upon completion of the trial or the occurrence of a serious adverse event.

### Intervention

We will regularly provide verbal and visual instructions to all subjects, standardize the movement, strengthen the concept of movement, and establish requirements for the amount and frequency of movement. We will according to the specific needs of each group of the experiment accordingly the intervention wording, to distribute it to all team members to participate in, and all the subjects will be asked to record the action content, and exercise duration/sports strength/sports venues, as well as their movement during or after personal feelings, etc. The specific exercise movements of the three positions of the new Baduanjin are shown in these figures (Figs. 3, 4 and 5).

**Fig. 3 Fig3:**
[figure not shown]
An improved version of the standing form Baduanjin consists of eight parts, which are: Tiger paws for sky, Drawing the bow, Reach for the stars with your hands, Look after conditioning body weakness, Drum position, The body stretch pull, The tiger pounced and Tip-toe position

**Fig. 4 Fig4:**
[figure not shown]
An improved version of the sitting form Baduanjin consists of eight parts, which are: Pushing up he sky to clear lung function, Use hand to massage forearm, Rub thoracoabdominal to heighten digestion, Bend over and rotate the hip joint, Bend your neck to extend your arm, The way you hold the ball, Throw a punch position and Stretch leg position

**Fig. 5 Fig5:**
[figure not shown]
An improved version of the lying form Baduanjin consists of eight parts, which are: Pushing up the sky to regulate the triple warmer, Use hand to massage thoracoabdominal, Rub your chest with hands, A massage abdomen position, Roll your hands and tum your head, Press and rub the rib, Supine bridge hip extension and Knee leg bending posture

#### Control group

Members of the CG will continue to receive their regular care or medication without intervention for exercise.

#### Modified baduanjin exercise group

IG participants will continue to receive their existing prescription medication, plus an exercise program for three months. IG’s exercise regimen is set to be once a day and twice a day. A steering committee of hospital specialists facilitates weekly training and education courses. Each session will be 60 min in length. Include (1) 10 min of warm-up exercise; (2) 40-minute sports training of Modified Baduanjin; (3) 10 min of relaxing stretching and cooling exercises. Under the doctor’s verbal and visual supervision, the exercise is conducted safely, and their exercise intensity and heart rate are monitored to prevent accidents and ensure the trial ran smoothly.

#### Traditional baduanjin exercise group

In addition to the 3-month exercise program intervention, TG participants did not alter their original prescription medications. The frequency of TG’s exercise is once per day, twice per day. The hospital’s experts will form a steering committee to facilitate weekly training and education courses for TG participants. Each session will be 60 min in length. Include (1) 10 min of warm-up exercise; (2) 40 min of traditional Baduanjin exercise training; (3) 10 min of relaxing stretching and cooling exercises. Patient surveillance and patient safety are used in the same way as IG.

#### Resistance exercise group

In addition to resistance training, participants in the RG will continue to take their prescribed medications for three months. We will report on resistance training involving the trapezius/deltoid/biceps/pectoralis major, rectus femoris, gluteus maximus, quadriceps femoris, gastrocnemius, and soleus in previous studies of COPD patients with improved lung and limb function. The intensity of resistance training will be divided into eight levels, with the resistance increasing as the level increases. Three times per week, RG will exercise for one hour. Specifically include: (1) 10 min of warm-up exercise, (2) can involve the above 10 muscles-based resistance training, lasting 40 min. (3) 10 min of related muscle relaxation. Patient surveillance and patient safety are used in the same way as IG.

#### Modified baduanjin exercise combined with the resistance exercise group

Participants in the IRG will continue to receive prescription medications in addition to three months of Modified Baduanjin and anti-resistance exercises. The exercise program of IRG is set as Baduanjin for 7 days a week and anti-resistance exercise for 3 days a week, with the corresponding exercise twice a day. In addition, once a week, patients will engage in a prescribed training exercise under the supervision of doctors in order to standardize and supervise their exercise. Each session will last 60 min and include: (1) a 10-minute warm-up starter; (2) a 20-minute Modified Baduanjin exercise, the operation is the same as IG group; (3) rest for 5 min. (4) anti-resistance exercise for 20 min. The operation is the same as the RG group. (5) 5 min of relaxation and cooling exercise.

### Advice to stay active

Throughout the duration of the trial, both experimental and control participants will be required to attend an educational course on IPF treatment in order to maintain their interest and keep them active. The course will concentrate on two aspects: exercise therapy regimen for IPF and the positive effects of exercise on IPF. All participants are required to attend and sign in for the twice-monthly online and offline classes. The doctors responsible for teaching the course ([name] and [name]) will strongly encourage all participants to complete the course and meticulously record the completion of everyone’s course. The purpose of the course is to encourage participants to participate more actively in the experiment’s launch and completion of the corresponding indicator detection, which will facilitate the experiment’s execution and receipt collection.

### Adherence to interventions

To let all subjects complete the test, we will organize experts on the subjects not less than once a week phone access, answer the questions according to measured by the number of treatment adherence, and compliance of index is set in greater than or equal to 85%, the equivalent of CG participants to answer questions not less than 11. For patients in the other intervention groups, compliance is quantified by the number of hospital-organized supervised training sessions they attended and the number of daily exercise logs they completed. Again, this compliance is set to at least 85% completion of the course or log.

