**Methods/design:**

A single-blind and randomized controlled trial is used to conduct this study, while the randomization list will be generated using a computerized random number generator and opaque sealed envelopes with group allocation will be prepared. It will be strictly followed to blind the outcome assessors. and until the experiment’s conclusion, participants won’t know which group they are enrolled in. Patients between the ages of 35 and 80 who have stable diseases and have not regularly practiced Baduanjin exercise in the past will be included. They are divvied up into the following five groups at random: (1) The conventional care group (control group, CG), (2) The traditional Baduanjin exercise group (TG), (3) The modified Baduanjin exercise group (IG), (4) The resistance exercise group (RG) (5) The modified Baduanjin exercise combined with resistance exercise group (IRG). Those CG participants only received the usual treatment, while TC, IG, and RG participants exercised 1 h twice a day for 3 months. MRG participants will have a 3-month intervention with 1 h of Modified Baduanjin Exercise and 1 H of Resistance Training for each day. Every week, all groups underwent will supervis one-day training, with the exception of the control group. The Pulmonary Function Testing (PFT), HRCT, and 6MWT are the main outcome variables. The St. George Respiratory Questionnaire and mMRC are used as secondary outcome measures.

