### Statistical analysis

The SPSS (version 23.0) is used for data management and statistical analysis. The kolmogorov-Smirnov test is used for normality test. The normality data are expressed as mean ± SD, and the skewness data are expressed as median and quartile spacing. An intention-to-treat analysis will be used to assign participants whether or not they complete the intervention. Lost result data will be processed using a mixed-mode approach. Each protocol is then examined, including only patients who completed all outcome measures and followed the intervention protocol. Comparisons of baseline differences between groups will be made using one-way analysis of variance (ANOVA) or nonparametric tests. The training-related effects are evaluated using a 2 × 2 ANOVA (group × time). Differences in each group of variables over time (time effect, from baseline to 3 months) will be assessed using either a paired T-test or a nonparametric test. To detect differences between categorical variables, the Chi-square test will be applied. Bilateral *P* values < 0.05 are considered significant. In addition, the effects of different interventions on Lung function have been found in previous studies, and disease severity may be an important factor. Therefore, in order to investigate differences in effectiveness based on disease severity, a pre-designated subgroup analysis will be conducted.

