Still, our study has some limitations. First of all, as a kind of exercise intervention, the Modified Baduanjin will inevitably fail to blind participants and doctors, which may lead to a certain degree of bias in the results. Lack of blinding may also contribute to sample shedding, with participants in different treatment groups experiencing varying levels of psychological impact, leading to the possibility of early withdrawal from the trial. Second, the focus of this study is given priority to home exercise intervention, the patient’s compliance may not be able to get a good guarantee, but the staff will promptly with the participants of this study via remote video and telephone contact, strengthen communication, supervision, and education curriculum implementation once a week, at the same time to test the normal; Lastly, the promotion of the Modified Baduanjin may be limited to some extent by the specificity of different populations as a result of regionalism, as different regions and populations have varying degrees of acceptance and recognition of the Modified Baduanjin.

In conclusion, this study introduced a Modified Baduanjin through three different forms (vertical, seated, horizontal) on the stability of IPF patients’ intervention of clinical trial plan, aims to investigate the lung function and limb function and role in IPF patients, as well as the influence of a single solution (including Modified Baduanjin and resistance training) and the benefits and drawbacks of the joint scheme. In addition, these results may provide clinicians and therapists with a new IPF rehabilitation protocol that is simple, safe, and effective.

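### The 85% compliance rule for the exercise arms is worded so that weekly class attendance alone can meet it, whatever home exercise was done

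*Protocol article*

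**What the plan says.** Under Adherence to interventions, the article states that in the exercise arms "compliance is quantified by the number of hospital-organized supervised training sessions they attended and the number of daily exercise logs they completed". The next sentence gives the cut-off: "Again, this compliance is set to at least 85% completion of the course or log". For the control group the same section uses weekly telephone contact: "compliance of index is set in greater than or equal to 85%, the equivalent of CG participants to answer questions not less than 11".

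Supervised training is weekly. The modified Baduanjin section says "A steering committee of hospital specialists facilitates weekly training and education courses", with a parallel statement for the traditional Baduanjin group. The combined-group section says that "once a week, patients will engage in a prescribed training exercise under the supervision of doctors". The abstract gives one supervised day a week for every group except control.

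The prescribed exercise is far more frequent, and its frequency is stated inconsistently. The abstract says of the single-modality exercise groups that "participants exercised 1 h twice a day for 3 months". The two Baduanjin sections each give both once and twice a day. The resistance section gives three sessions a week. The combined-group section gives Baduanjin every day and resistance on three days, each twice a day.

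The limitations paragraph of the Discussion adds that "the focus of this study is given priority to home exercise intervention, the patient’s compliance may not be able to get a good guarantee".

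The Statistical analysis section plans an intention-to-treat analysis and then a second analysis "including only patients who completed all outcome measures and followed the intervention protocol". The Data analysis section repeats this in near-identical terms.

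**The concern.** The two counts are joined by *and* where they are introduced and by *or* where the threshold is set. Taken at its word, the threshold lets the supervised class stand in for the whole programme. The class is the smallest part of the prescribed exercise. The home part is the larger, and it is the part the authors themselves say they cannot guarantee. A participant who came every week and did nothing at home would be classed as compliant.

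The log route has a related weakness: it counts logs completed, not sessions performed. The literal rule also works in reverse, since full self-reported logs with no class attended would pass.

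Two results are at stake. The reported adherence rate could be high while little of the programme was delivered. The per-protocol comparison, if it uses this rule, could include participants who were largely unexercised and so would not describe the programme as prescribed.

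**Working it through.** **Inputs**
- Threshold: 85% (Adherence to interventions).
- Supervised sessions: one a week (abstract; modified and traditional Baduanjin sections; combined-group section).
- Duration: three months, taken as 12 or 13 weeks (assumption).
- Prescribed frequency: the stated alternatives, used side by side without choosing between them.
- One log per day (assumption).

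**Step 1. The article's own figure.** The control group's 85% is equated with at least 11 weekly contacts.
- 12 weeks: 0.85 × 12 = 10.2, rounded up to 11.
- 13 weeks: 0.85 × 13 = 11.05, strictly rounded up to 12 (11/13 = 84.6%).

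The stated 11 reproduces at 12 weeks. The same count applies to weekly classes, so the course route needs 11 of 12 or 12 of 13.

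**Step 2. Share of prescribed exercise done by someone who passes on classes alone.** Share = classes needed ÷ sessions prescribed, counting the classes as part of the prescription.

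| Stated frequency | 12 weeks | 13 weeks |
|---|---|---|
| Twice daily | 11/168 = 6.5% | 12/182 = 6.6% |
| Once daily | 11/84 = 13.1% | 12/91 = 13.2% |
| Three times a week | 11/36 = 30.6% | 12/39 = 30.8% |
| Combined group, both components counted (14 + 6 = 20 a week) | 11/240 = 4.6% | 12/260 = 4.6% |

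In the combined group, if only the Baduanjin sessions are counted (14 a week), the twice-daily row applies.

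**Step 3. If the classes come on top of the prescription.** The combined-group section can be read this way. The denominator then grows by one session a week:
- Twice daily: 11/180 = 6.1%; 12/195 = 6.2%.
- Once daily: 11/96 = 11.5%; 12/104 = 11.5%.
- Three times a week: 11/48 = 22.9%; 12/52 = 23.1%.
- Combined group, both components: 11/252 = 4.4%; 12/273 = 4.4%.

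**Step 4. If both counts were required.** Besides the classes, a participant would need 0.85 × 84 = 71.4, so 72 of 84 daily logs, or 0.85 × 91 = 77.35, so 78 of 91. Under the literal *or*, no logs are needed.

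**The case against.** The strongest reply is that the authors meant both counts. The sentence before the threshold joins them with *and*, the threshold sentence refers back to that measure, and in loosely edited English *or* may mean 85% of whichever is being counted. This reading is possible, so the text does not establish that an either-or rule was intended. But the sentence that sets the threshold says *or*, and nothing elsewhere resolves it. The correction is the same under both readings.

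Second, the Statistical analysis and Data analysis sections do not cite the 85% rule, and an analysis plan that is not shown may define the per-protocol set differently. This stands: the link is an inference, resting on 85% being the only adherence criterion in the article.

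Third, the percentages describe a worst case with no home exercise, and nothing in the article says how often that would happen. This also stands. They show what the rule permits, not what is expected.

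Fourth, the Safety section says all exercise is supervised, which would leave no unsupervised home exercise. That conflicts with the weekly supervision stated elsewhere and with the Discussion. The passages need reconciling, and this one does not rescue the rule.

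Fifth, *course* might mean the twice-monthly education course under Advice to stay active, which controls also attend. That reading would make the rule weaker, not stronger.

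A reader might infer more than the article supports:
- *A null result could not be interpreted.* The Intervention section asks participants to record what they did and for how long, so exercise performed can be examined whatever the compliance label.
- *An empty log counts as completed.* The article does not say so; it says only that the count is of logs.
- *The control group should be reclassified by whether its members took up exercise.* Controls have no programme to follow, so a different measure is unavoidable. The general request for exercise records is not tied to this group, and no section specifically provides for recording such uptake.

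**Conclusion.** The point holds as a badly worded threshold. Read literally, the rule can classify an exercise-arm participant as compliant on 11 of 12 or 12 of 13 weekly classes. That is about 6.5% of prescribed sessions under a twice-daily regimen, 13% under once daily and 31% under three times a week, and lower if the classes are additional to the prescription. These figures assume 12 to 13 weeks, one class a week and no home exercise.

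The direct effect is on reported adherence. The effect on the per-protocol analysis is inferred. A reader might take the main comparison to be compromised as well, but the intention-to-treat analysis includes participants whether or not they complete the intervention, so the rule does not touch it. The wording should be corrected because a stated threshold that can label largely unexercised participants as compliant is more than a detail left out of an article.

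**What to change.** In Adherence to interventions, require at least 85% of supervised sessions **and** at least 85% on the log component. Define the log component as exercise sessions recorded as performed, divided by sessions prescribed for that arm, using the records described in the Intervention section. Report sessions performed by arm alongside the compliance rate.

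This depends on one prior step. The denominator does not exist until the conflicting frequencies in the abstract and the arm-specific intervention sections have been reconciled. Which frequency applies is for the investigators to state.

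The control group's telephone-based measure can stay as it is. The Trial status section says recruitment is complete, so the definition should be settled before the adherence and per-protocol results are analysed.

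The change needs no new data, provided the exercise records were kept as described. Its costs are a smaller per-protocol set and a lower reported adherence rate.
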